### Sensitivity and subgroup analyses

We will perform several sensitivity and subgroup analyses to assess the robustness of the findings of our primary analysis to different assumptions:

We will explore the impact of using a wider definition of MI and stroke, including ICD-10 codes for acute coronary syndromes and transient ischaemic attacks. This will include events that have potentially been missed by our main definition and assess how sensitive our findings are to the definition of MI and stroke.We will explore the impact of widening the microbiological definition of UTI to bacterial growth of a single organism of ≥1x10^7^ CFU per litre irrespective of WCC.We will differentiate first-ever MI or stroke from recurrent events, and report risk estimates separately. This analysis will exclude individuals with a PEDW record of an event before the observation period, and include only those who have their first ever event during the observation period.We will extend the prerisk period to 14 days. Some individuals may have had an UTI for several days prior to diagnosis, and so an acute MI or stroke during this time may relate to exposure but without a prerisk period, would count towards the baseline period.We will repeat the analysis excluding individuals who died within 30 days of an event to examine the potential effect of an event dependent observation period.We will restrict the definition of UTI to include only antibiotic prescriptions for nitrofurantoin (currently recommended first-line therapy) to explore whether the choice of antibiotic impacts the findings.We will use interaction terms to assess the impact of specific bacterial organisms on the relationship between UTI and MI or stroke.We will examine whether the COVID-19 pandemic may affect our findings by (1) excluding individuals whose MI or stroke occurred in 2020, and (2) including an interaction term to explore whether the association between exposure and outcome differs in 2020 vs pre-2020.We will include an interaction term to explore whether the association between exposure and outcome differs in those with and without a history of diabetes, given its potential role as a risk factor of both UTI and MI/stroke.

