	As both MI and stroke have relatively high death rates, the length of the observation period is dependent on events, and no further exposures are possible after death.	Use an event-dependent observation period model extension^38^ and conduct a sensitivity analysis that repeats the analysis, excluding individuals who died within 30 days of the event.	Bruer *et al* used the event-dependent observation period model extension in their study on the association between antipsychotic drugs and myocardial infarction.^39^ Langan *et al* studied the risk of stroke following herpes zoster. They conducted a sensitivity analysis excluding individuals who died within 90 days of stroke.^40^
Event rates are constant within defined periods	MI and stroke are more common in older individuals and may be affected by seasonal changes.	Control for age and season effects.	Grave *et al* studied the association between seasonal influenza vaccination and Guillain-Barré syndrome. They adjusted for calendar month, as the vaccinations are seasonal by design.^41^ In a study of the association between chickenpox and stroke, Thomas *et al* adjusted for age in 5-year age bands.^42^
Events are independently recurrent or rare.	MI and stroke are not independent: once an individual has a first event, they are more likely to have a second.	Study first events only.	Langan *et al* began the observation period 12 months into follow-up time to ensure first stroke events had been correctly identified.^40^

MI, myocardial infarction; UTIs, urinary tract infections.

A diagrammatic representation of observation time for an individual in the proposed SCCS design is given in figure 1. Risk periods start on the date of an UTI and end 90 days later. The date of an UTI is the earliest date of occurrence of any of the events necessary for each different UTI definition. For example, the definition of UTI in our primary analysis is a combination of an UTI-related diagnostic code and antibiotic prescription in WLGP data and a urine culture result that supports a diagnosis of UTI in the WRRS data, occurring within a 7-day window. In this case, the date of the UTI would be the date of whichever of the following events occurred first: UTI-related diagnostic code, antibiotic prescription, supporting urine culture.

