### Statistical analysis

We will describe the demographics of the study population, such as age and sex distribution, medical history and prescribed medication, using means and SDs for continuous variables, and frequencies and proportions for categorical variables. For each analysis, we will use conditional logistic regression to estimate IRRs, with 95% CIs, for the risk of acute MI or stroke in prerisk and risk periods compared with baseline periods. We will include only individuals who have experienced both the outcome and the exposure, and will include only the first acute MI or stroke diagnosis in the observation period. The IRRs will be adjusted for time-varying confounders: age, season and year of UTI diagnosis. Year of UTI diagnosis is included because diagnostic and coding practices may have changed over time as a result of guidance and awareness around microbial resistance. Adjusted IRRs will be reported for the risk of acute MI or stroke at 1–7, 8–14, 15–28 and 29–90 days after UTI. We will conduct the analysis in R, using the SCCS package. We will report the findings in accordance with REporting of studies Conducted using Observational Routinely-collected Data (RECORD) and STrengthening the Reporting of OBservational studies in Epidemiology (STROBE) guidelines.

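### As specified, the first-ever versus recurrent sensitivity analysis contains no recurrent events, so only one of its two promised estimates can be reported

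*Protocol article*

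**What the plan says.** Three places in the protocol article bear on this.

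- **Sensitivity and subgroup analyses, third item.** The promise is "We will differentiate first-ever MI or stroke from recurrent events, and report risk estimates separately". The sentence after it reads: "This analysis will exclude individuals with a PEDW record of an event before the observation period", and adds that the analysis will "include only those who have their first ever event during the observation period".
- **Statistical analysis.** For each analysis, the investigators "will include only the first acute MI or stroke diagnosis in the observation period".
- **Study design, Table 1.** On the assumption that events are independently recurrent or rare, the table states that "MI and stroke are not independent: once an individual has a first event, they are more likely to have a second". The remedy given is "Study first events only".

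The list of sensitivity and subgroup analyses is introduced as a test of how robust the primary findings are to different assumptions. No figure is given for how many cases are first-ever and how many recurrent.

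**The concern.** The item commits to two estimates, one for first-ever events and one for recurrent events, but the eligibility rule attached to it admits only first-ever cases. The general rule of one event per person rules out the other source of recurrent events. An analyst who follows the text has no population from which to estimate the recurrent IRR.

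What is at stake is what this item can report. The first-ever estimate would have only the main estimate to stand beside, and the main estimate is a mixture that includes the same first-ever cases. A reader might take agreement between the two as evidence that prior events make no difference, when comparing a subset with the whole mutes any difference that exists. An analyst might also define a recurrent group after seeing the data, and the choice of definition would then not be prespecified.

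**Working it through.** No figure in the article can be reproduced here. The main check is to trace the rules.

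**Step 1: how a recurrent event could enter.**

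| Route | Rule that applies | Result |
|---|---|---|
| (a) First event within observation, in a person with an earlier PEDW-recorded event | Exclusion in the third sensitivity item | Removed |
| (b) Second or later event within observation | First-event-only rule in Statistical analysis, consistent with the Table 1 remedy | Removed |

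No other route leads to an identified recurrent event. Someone whose earlier event was recorded only outside PEDW would stay in, but would be classed as first-ever. The item therefore yields one estimate.

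**Step 2: what the main analysis contains.** The main analysis takes the first event within observation and states no exclusion for earlier events. The extra exclusion in the sensitivity item has a purpose only if the main case set keeps people with earlier events. The main estimate is therefore a mixture of first-ever and recurrent cases, and the comparison left is first-ever against all.

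**Step 3: how far that comparison is diluted.** Let b_f and b_r be the log-IRRs in first-ever and recurrent cases, and p the share of information from recurrent cases. As an approximation with linear pooling:

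- main estimate ≈ (1 − p)·b_f + p·b_r
- main minus first-ever ≈ p·(b_r − b_f)

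The visible difference is the fraction p of the true one, whatever the two log-IRRs are. For illustration, assume b_f = 0.10 and b_r = 0.50, a true difference of 0.40:

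| Assumed p | Main estimate | Main minus first-ever |
|---|---|---|
| 10% | 0.9×0.10 + 0.1×0.50 = 0.14 | 0.04 |
| 20% | 0.8×0.10 + 0.2×0.50 = 0.18 | 0.08 |
| 30% | 0.7×0.10 + 0.3×0.50 = 0.22 | 0.12 |

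Both the log-IRRs and p are assumptions. Table 3 reports a history of coronary heart disease in 21.5% of MI cases, but that is not a history of hospital-recorded MI and cannot be used to set p.

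**Step 4: which earlier event should define recurrence.** The article treats MI and stroke as separate case groups. It reports 51 656 MI cases, 58 146 stroke cases and 105 930 unique individuals, so 51 656 + 58 146 − 105 930 = 3 872 people are in both. If any earlier MI or stroke counted as prior history, a first-ever MI after an earlier stroke would be labelled recurrent. The split therefore has to be made on the same outcome.

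**The case against.** The strongest reply is that the second sentence may define only the first-ever arm, with the recurrent arm understood as everyone else in the main case set. The same PEDW flag identifies both groups, and a journal article is condensed. That reading is possible. But the sentence refers to the analysis just described, which is the one meant to give both estimates, and no recurrent population is defined anywhere. On this reading the recurrent arm is undefined rather than empty, and the same clarification is needed.

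Second, the item promises separate estimates, not a test of their difference. Where the investigators want a formal contrast they say so, as with the interaction terms for organism, for 2020 against earlier years, and for diabetes. Setting a restricted subset beside the main result is ordinary practice for a robustness check, and the article does so for deaths within 30 days and for events in 2020. This stands: the missing interaction is not itself a fault. It is only the natural form of the repair. The missing second estimate remains.

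Third, a reader might infer that the primary analysis fails to apply the Table 1 remedy because people with earlier events stay in it. The article does not support so strong a reading. Counting one event per person within observation addresses repeat events there, and the stricter first-ever restriction is what this sensitivity item adds.

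**Conclusion.** The point holds for the analysis as specified: it gives a first-ever estimate and no recurrent one. This rests on the wording alone and needs no numerical assumption. The size of the dilution in the remaining comparison does rest on assumptions. The visible difference is about p times the true one, and the article gives no value for p.

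Three stronger readings are not supported:

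- A reader might infer that no recurrent estimate is obtainable at all. The main case set appears to keep people with earlier events, so the data could provide one; the plan does not ask for it.
- A reader might infer that the item was meant to answer whether prior events modify the effect of UTI, or that the future trial depends on it. The stated purpose is robustness, the objectives do not mention prior events, and the dissemination section ties the trial to an association between UTI and either outcome.
- A reader might infer that the exclusion catches every earlier event. It catches only those in PEDW.

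The primary estimate, the objectives and the power statement are unaffected. This is a correction to one sensitivity item, worth making before analysis because it determines what that item can report.

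**What to change.** Replace the exclusion with a split. Divide the main case set by whether PEDW holds an earlier record of the same outcome from before the person's observation began: MI for the MI analysis, stroke for the stroke analysis. Analyse the first event within observation in both strata, which keeps the one-event-per-person rule. Report the IRR and 95% CI in each stratum, with an exposure-by-history interaction of the kind already planned for diabetes.

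The cost is the rewording of one item and one extra model term. The earlier PEDW records are already needed for the planned exclusion. The recurrent stratum will be imprecise, and the report should say so.

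If the investigators do not want the recurrent estimate, the alternative is to delete the promise of separate estimates and call the item a first-ever-only sensitivity analysis, to be read beside the main result on the understanding that the main case set contains it. That costs one sentence.

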We will use the SAIL Databank to access the following linked data: Welsh Longitudinal General Practice data (WLGP), Patient Episode Database for Wales (PEDW), Welsh Results Reporting Service (WRRS). The WLGP contains data from 84% of general practices in Wales, consisting of longitudinal data for 2.6 million Welsh residents, representing 84% of the population.^24^ Demographic data, clinical diagnoses and prescription data are included. The PEDW contains International Classification of Disease version 10 (ICD-10) coded diagnoses for admissions to any Welsh hospital.^25^ The WRRS contains data on all tests requested from primary and secondary care National Health Service (NHS) Wales organisations processed and analysed in NHS Wales laboratories, including requests for urine microscopy, culture and antibiotic susceptibilities.^26^ Data are available from the data sources at varying times based on when clinical information systems began, with data quality improving over time. As such, for our study, based on our approvals and where the data sources have consistent coverage and quality, we will be using them between 1 January 2010 and 31 December 2020.

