**Figure 1 F1:**
[figure not shown]
Diagrammatic representation of observation time for an individual in the proposed self-controlled case series design. MI, myocardial infarction; UTI, urinary tract infection.

Individuals can have more than one UTI during the observation period, and therefore can have more than one 90-day risk period. Where risk periods overlap, the later period takes precedence, and the earlier period is shortened. There will be a prerisk period of 7 days before the risk period, to allow for the situation where an individual has an UTI for several days prior to consultation, so events in the prerisk period are not erroneously attributed to the baseline period.

Baseline periods are all times outside of the risk and prerisk periods. The study period is from 1 January 2010 to 31 December 2020. The observation period is different for each individual. It generally follows the study period but may start later for some individuals who were not Welsh residents at the start of the study period but became so later, or who turned 30 years of age sometime during the study period. Similarly, the observation period may end before the study period when individuals moved out of Wales or died.

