**Figure 2 F2:**
[figure not shown]
Case selection process. *Individuals appear and are counted in both the stroke and MI datasets if they had both an MI and a stroke event within the study period. MI, myocardial infarction; PEDW, Patient Episode Database for Wales; SAIL, Secure Anonymised Information Linkage; WLGP, Welsh Longitudinal General Practice data; WDSD, Welsh Deographic Service Dataset.

The mean length of observation (study entry to study exit) of stroke cases was 2796 days for females and 2981 days for males. For MI cases, 2981 for females and 3251 for males. History of diagnoses and prescription drugs is taken from all health records available for each individual. Health data is available for a median of 13 years (25–75th centiles 8–16) prior to the study start.

Characteristics of cases, including a history of diagnoses and prescription drugs prior to an event, smoking status, Welsh Index of Multiple Deprivation version 2019 and electronic Frailty Index are given in table 3.

**Table 3 T3:** Characteristics of cases of stroke and MI

Characteristic	Stroke	MI
Sex (% male)	49.4	62.8
Age of males (mean (25th, 75th centiles))	74 (64, 82)	69 (59, 78)
Age of females (mean (25th, 75th centiles))	79 (69, 87)	77 (66, 85)
Welsh Index of Multiple Deprivation (WIMD) 2019 quintiles*		
1 (least deprived)	19.8	20.6
2	20.8	20.5
3	20.3	20.9
4	20.4	20.1
5 (most deprived)	18.6	17.9
Current smoker (%)	19.8	24.2
electronic Frailty Index (mean (SD))	0.16 (0.12)	0.15 (0.12)
Prescribed lipid-lowering drugs (%)	49.0	49.6
Prescribed aspirin (%)	43.7	41.3
Prescribed hypertensive drugs (%)	59.1	55.1
Prescribed beta blockers (%)	39.6	37.3
Chronic kidney disease (%)	20.9	18.9
COPD (%)	9.9	10.9
Asthma (%)	15.1	16.0
Hypertension (%)	51.2	46.2
Diabetes (%)	19.4	20.7
Cardiovascular disease (%)	56.4	53.4
Coronary Heart Disease (%)	15.9	21.5
Atrial fibrillation (%)	16.0	8.7
Heart failure (%)	8.4	8.6
Peripheral vascular disease (%)	7.2	7.7
Angina (%)	11.3	16.0
Transient ischaemic attacks (%)	9.4	5.0
Total no of cases	58 150	51 659

*LSOA version 2011 and WIMD version 2019

COPD, Chronic Obstructive Pulmonary Disease; LSOA, Lower Super Output Area; MI, myocardial infarction.

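### The first-ever event analysis finds earlier MI or stroke in Welsh hospital records alone, so some recurrent cases will be classed as first-ever

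*Protocol article*

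**What the plan says.** The protocol article, Sensitivity and subgroup analyses, sets the aim: "We will differentiate first-ever MI or stroke from recurrent events, and report risk estimates separately". It then gives the rule: "This analysis will exclude individuals with a PEDW record of an event before the observation period". The analysis is to "include only those who have their first ever event during the observation period". PEDW is the only source named for establishing prior history.

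Four other places bear on this:

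- **Data** describes PEDW as holding "coded diagnoses for admissions to any Welsh hospital". Of the linked general practice data (WLGP) it says: "Demographic data, clinical diagnoses and prescription data are included".
- **Study design**, below Figure 1, allows a later start of observation for people "who were not Welsh residents at the start of the study period but became so later".
- **Summary of cases** says of the descriptive data: "History of diagnoses and prescription drugs is taken from all health records available for each individual". Records go back a median of 13 years before study start (25th–75th centiles 8–16).
- **Study design, Table 1** notes that a first MI or stroke makes a second more likely, and answers: "Study first events only". Statistical analysis applies this as the first event within the observation period, which need not be the first in the person's life.

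**The concern.** The label first-ever promises more than the rule can deliver. Absence of a Welsh hospital record is not absence of an earlier event. The group can be cleaner at little cost, because GP diagnoses are already linked and already used to describe case history.

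The contrast between first-ever and recurrent cases is at stake. If the IRR differs between them, unrecognised recurrences blur that difference and the first-ever estimate no longer describes the group it names.

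**Working it through.** The protocol states no figure for this analysis, so there is nothing to reproduce. The check has two parts.

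**1. Who passes the rule**

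| Earlier event | In PEDW? | In WLGP? | Classed under the stated rule |
|---|---|---|---|
| Admitted to a Welsh hospital within the record period | Yes | Possibly | Not first-ever (correct) |
| Treated outside Wales | Not expected | Possibly | First-ever (wrong) |
| Before moving to Wales | Not expected | Possibly, as diagnosis or history | First-ever (wrong) |
| Not admitted, known to the GP only | No | Yes | First-ever (wrong) |

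The primary exposure needs a GP diagnostic or symptom code and a GP antibiotic prescription (Exposure; Table 2). Every case in the primary analysis therefore has linked GP data that could be searched.

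**2. Illustrative size**

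Inputs:

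- Risk window of 90 days (Exposure).
- Mean observation of 2981 days (Summary of cases; the figure for male stroke cases and female MI cases), so r = 90/2981 = 0.0302.
- Share q of the first-ever group that is truly recurrent. *Assumed*, 2–20%.
- IRRs in truly first-ever (a) and truly recurrent (b) cases. *Assumed*.

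For a case with one risk window and rate ratio ρ, the chance that the event falls in the window is π(ρ) = ρr / (ρr + 1 − r). In the mixed group it is π_m = (1 − q)π(a) + qπ(b). The IRR that would be read is [π_m / (1 − π_m)] × (1 − r)/r.

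Example with a = 1.3, b = 2.0, q = 0.10: π(a) = 0.0389, π(b) = 0.0586, π_m = 0.0409, IRR read = 1.369.

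| q | a = 1.3, b = 1.3 | a = 1.3, b = 1.6 | a = 1.3, b = 2.0 | a = 1.6, b = 1.3 |
|---|---|---|---|---|
| 2% | 1.300 | 1.306 | 1.314 | 1.594 |
| 5% | 1.300 | 1.315 | 1.334 | 1.585 |
| 10% | 1.300 | 1.330 | 1.369 | 1.570 |
| 20% | 1.300 | 1.360 | 1.438 | 1.540 |

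For a = 1.3 and b = 1.0, simple linear mixing is close enough: 0.95 × 1.3 + 0.05 × 1.0 = 1.285, and 0.85 × 1.3 + 0.15 × 1.0 = 1.255.

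**Against sampling error.** Sample size and power states 90% power for an IRR of 1.3 at alpha 0.05. Taking that as two-sided, SE(log IRR) ≈ ln(1.3)/(1.96 + 1.28) = 0.262/3.24 ≈ 0.081.

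- a = 1.3, b = 1.0, q = 5–15%: shifts of ln(1.3/1.285) = 0.012 and ln(1.3/1.255) = 0.035, about 0.14 to 0.44 of one SE.
- a = 1.3, b = 2.0, q = 10%: ln(1.369/1.3) = 0.052, about 0.64 of one SE.
- a = 1.3, b = 2.0, q = 20%: ln(1.438/1.3) = 0.101, about 1.25 SE.

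The first-ever group is a subset, so its own SE would be larger and these ratios smaller.

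**The case against.** **The rule is coherent.** Outcomes are defined by inpatient ICD-10 codes in PEDW (Outcomes), so using PEDW for earlier events puts prior and current events on one footing. That stands as a reason for the choice. It supports a label such as first hospital-recorded event, but does not make a case first-ever.

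**GP history codes can be imprecise.** It is tempting to say that a false positive merely costs one case. That holds only if the coded person is dropped. Since separate estimates are promised, a wrong GP history code could move a true first-ever case into the recurrent group and contaminate it. This stands, and the fix has to allow for it.

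**A reader might infer that the independence assumption goes unchecked.** The documents do not support that. Table 1 concerns dependence between a person's successive events, and the main analysis already takes one event per person. Earlier history is fixed before observation starts, and the design conditions out fixed characteristics. What remains is mainly whether the IRR differs by prior history, which is a subgroup question.

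**A reader might infer that this rule builds in agreement between the first-ever and main results.** The first-ever group is a subset of the main population under any definition, so some agreement is inherent. Adding GP codes does not remove it.

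**A reader might see a contradiction with Table 3.** Using all records to describe cases does not commit the protocol to the same source for this subgroup. It shows only that the data are at hand.

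**A minimum look-back might seem necessary.** The study of stroke after herpes zoster cited in Table 1 began observation 12 months into follow-up. With a median of 13 years of prior data, a 12-month requirement would add little for most cases. That median is not specific to PEDW, however, and does not settle the position of people who moved to Wales, whose number is not given.

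**Conclusion.** The point holds as a limited improvement to one sensitivity analysis. As written, the rule admits some recurrent cases to the first-ever group. Where the IRR differs by prior history, the first-ever estimate moves towards the recurrent one. Where it does not, there is no bias, so it would be wrong to say that the two groups are always drawn together.

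The size cannot be derived from the document: both the misclassified share and the two IRRs are assumptions. Most of the illustrated shifts are well under one standard error. Only the most extreme combination, 20% misclassified with IRRs of 1.3 and 2.0, exceeds one. The effect is probably small, and the primary analysis is unaffected.

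**What to change.** Define first-ever as no MI or stroke code in PEDW, and no MI or stroke diagnosis or history code in WLGP, before the observation period.

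For the recurrent estimate, keep the cases with a PEDW-confirmed earlier event as the recurrent group, or report that group under both definitions. Imprecise GP history codes then do not contaminate it.

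If GP codes are not used, rename the group *first event recorded in Welsh hospital data* and interpret it as such.

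The cost is one GP code list applied to data already linked, and some true first-ever cases lost to imprecise history codes in this one analysis. The change narrows the gap without closing it: an earlier event that appears in neither source will still be missed, and the documents do not say how fully WLGP holds events from before a move to Wales.

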### Exposure

The exposure of interest is an UTI. The risk period is 0–90 days following an UTI. This period was chosen as previous research has shown an increase in acute MI and stroke risk in the 1–90 days following an UTI.^6^ There will be a prerisk period of 7 days before the risk period, to allow for the situation where an individual has an UTI for several days prior to consultation, so events in this period are not erroneously attributed to the baseline period. Individuals can be exposed to an UTI more than once during the observation period. Each exposure will be followed by the same 90-day risk period. Baseline periods are all other times.

To ascertain UTI, we developed definitions that reflected the Public Health Wales Microbiology Division’s standard operating procedure for the investigation of urine.^36^ These procedures are followed by NHS microbiology laboratories across Wales. For each definition, the data sources required and the clinical scenario represented is summarised in table 2, and the code lists used are given in online supplemental material B–D. In our primary analysis, an individual will be regarded as being exposed to an UTI if the following events occur within a 7-day window:

A General Practice (GP) record of an UTI diagnostic or symptom code.A GP record of an antibiotic prescription.A microbiology record of a urine sample with bacterial growth of a single organism of ≥1x10^8^ colony-forming units (CFU) per litre and white cell count (WCC)≥1x10^8^/L. If there are two organisms grown, both must demonstrate growth of ≥1x10^8^ CFU per litre. More than two organisms will be regarded as mixed growth and thus not supportive of an UTI diagnosis. In a sensitivity analysis, we will widen the microbiological criteria and include all urine samples with bacterial growth of a single organism of ≥1x10^7^ CFU per litre, irrespective of the WCC.

**Table 2 T2:** Definitions of UTI for primary and secondary analyses. As the UTI definitions are combinations of two or more components, the start of the risk period is defined as the date of the earliest component

	UTI-related read code in GP data (online supplemental material B)	Antibiotic prescription in GP data (online supplemental material C)	UTI-related ICD-10 code in PEDW (online supplemental material D)	Urine culture results in WRRS	Time frame	Clinical scenario

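### The nitrofurantoin-only run gives no IRR for other antibiotics and no test of a difference, so it answers the antibiotic-choice question only in diluted form

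*Protocol article*

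**What the plan says.** The section on sensitivity and subgroup analyses introduces its list as a means "to assess the robustness of the findings of our primary analysis to different assumptions". One item will "restrict the definition of UTI to include only antibiotic prescriptions for nitrofurantoin (currently recommended first-line therapy) to explore whether the choice of antibiotic" makes a difference; its stated reason in full is "to explore whether the choice of antibiotic impacts the findings".

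In the primary definition (Exposure section and Table 2) the antibiotic component is simply "A GP record of an antibiotic prescription", taken from a code list. Every nitrofurantoin episode that meets the other criteria is therefore already in the primary exposure.

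Three other items in the same list handle effect modification with a model term:

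- Organism: "We will use interaction terms to assess the impact of specific bacterial organisms on the relationship between UTI and MI or stroke".
- Calendar period: "including an interaction term to explore whether the association between exposure and outcome differs in 2020 vs pre-2020".
- Diabetes: "We will include an interaction term to explore whether the association between exposure and outcome differs in those with and without a history of diabetes".

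No such term is planned for antibiotic, and no IRR is planned for episodes treated with other drugs.

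Two further statements bear on the restricted run. Baseline is all time outside risk and prerisk periods (Study design). The Exposure section also accepts, when it explains secondary analysis 5, that UTIs diagnosed in hospital probably fall into baseline in the primary analysis because they do not meet that definition.

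**The concern.** Whether antibiotic choice matters is a question about nitrofurantoin against the alternatives. The planned run yields one new number, the IRR after nitrofurantoin-treated UTIs. The natural thing to set beside it is the primary IRR, which mixes those same episodes with the rest. This has three consequences.

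1. The visible gap is smaller than the real one, and it shrinks as nitrofurantoin becomes more common.
2. The restricted run rests on fewer cases. A non-significant IRR may reflect lost precision alone.
3. UTIs treated with other antibiotics no longer meet the definition. Unless they are handled explicitly, their risk periods become baseline time for anyone who stays in the run.

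At stake is the interpretation of one exploratory analysis. A reader could take two similar IRRs as evidence against an antibiotic effect, or a lost significance as evidence for one. The planned output would support neither reading.

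**Working it through.** **The plan's own figure first.** Sample size and power states 90% power for an IRR of 1.3 at alpha 0.05, with 10% exposed and a 90-day window. I used the signed-root-likelihood formula for the self-controlled case series without age effects:

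- n = (z_α + z_β√B)² / A
- A = 2[q·ln R − ln(R·r + 1 − r)]
- B = (ln R)²·q(1 − q)/A
- q = R·r/(R·r + 1 − r), with r = 90/mean observation days

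For MI, the sex-weighted observation time is 0.628 × 3251 + 0.372 × 2981 = 3151 days, so r = 0.0286. Exposed cases are 0.10 × 51 656 ≈ 5166. Two-sided power is 91.9%. For stroke (2887 days, about 5815 exposed) it is 95.9%. With the full 4018-day study period in place of mean follow-up, the values are 84.9% and 88.7%. The stated 90% is consistent with these and is not in dispute.

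**Dilution.** Let p be the share of UTI episodes treated with nitrofurantoin (not given; assumed 0.3 to 0.9). With equal risk windows, the pooled IRR is approximately p·IRR_N + (1 − p)·IRR_O. On the log scale:

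ln IRR_N − ln IRR_pooled ≈ (1 − p)(ln IRR_N − ln IRR_O)

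*Example with assumed IRRs 1.3 and 1.8, p = 0.5.* Pooled = 0.5 × 1.3 + 0.5 × 1.8 = 1.55. The visible ratio is 1.3/1.55 = 0.84, against a true ratio of 1.3/1.8 = 0.72. On the log scale, 0.176/0.325 = 54% remains.

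*Second example, for MI.* Assumed IRRs are 1.2 and 1.6 (true ratio 0.75), with 5166 exposed cases, one 90-day window each and r = 90/3100. Each log IRR has SE = 1/√(n·q(1 − q)).

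| p | Visible ratio | Share of log contrast | Expected \|z\|, two IRRs read as independent | Expected \|z\|, nested variance | Expected \|z\|, direct contrast | Power, direct contrast |
|---|---|---|---|---|---|---|
| 0.3 | 0.81 | 73% | 1.35 | 1.73 | 1.80 | 44% |
| 0.5 | 0.86 | 53% | 1.19 | 1.89 | 2.01 | 52% |
| 0.7 | 0.91 | 33% | 0.81 | 1.74 | 1.89 | 47% |
| 0.9 | 0.97 | 11% | 0.30 | 1.14 | 1.28 | 25% |

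The nested-variance column uses Var = SE_N² − SE_pooled². It shows that the information is not destroyed. It is lost when the two IRRs are read side by side as if they were independent.

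**Precision of the restricted run.** If exposed MI cases fall in proportion to p, power for a nitrofurantoin IRR of 1.3 is 47%, 67%, 81% and 89% at p = 0.3, 0.5, 0.7 and 0.9.

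**Baseline contamination.** Suppose an individual has k UTIs treated with other antibiotics, each with IRR_O, and their risk windows fall into baseline. The baseline fraction affected is f = 90k/(3100 − 97), where 97 is the 90-day risk period plus the 7-day prerisk period. The baseline rate is multiplied by 1 − f + f·IRR_O.

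- k = 1, IRR_O = 1.3: factor 1.009, so a true IRR of 1.3 reads 1.29.
- k = 3, IRR_O = 2.0: factor 1.090, so a true IRR of 1.3 reads 1.19.

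**The case against.** The strongest reply is that the list exists to test robustness. On that reading, the item asks only whether the UTI association persists under one uniform first-line treatment, and restriction answers that. Where the authors want effect modification they say the association may differ, and they specify an interaction. Nitrofurantoin against other drugs is not among the three objectives. The article is also condensed, and supplementary tabulations are often left to an analysis plan.

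Part of this stands. Restriction is a legitimate robustness check. Sharing data with the primary result is normal in sensitivity analyses: excluding early deaths or 2020 events does the same. Overlap alone is not the fault. What remains is that the article states both a method and a reason, the reason names the choice of antibiotic, and the method has no arm for the alternatives.

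A reader might go further and infer that the run can reveal nothing about antibiotic choice. The documents do not support that. A diluted signal remains, and with the nested variance it could be tested almost as well as the direct contrast; no such test is planned. A reader might also infer that the authors intend to conclude from overlapping intervals that antibiotic choice is irrelevant. The protocol states no such rule and says only that it will explore the question. The comparison with the primary result is itself implied by the section's purpose and is not written out.

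The direct contrast has limits too. Its power in the example is only 25% to 52%, and a difference could reflect which UTIs receive nitrofurantoin.

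**Conclusion.** The point holds in a limited form. As described, the antibiotic analysis supplies no estimate for UTIs treated with other drugs and no test of a difference. Its implied comparison shows about (1 − p) of the true log contrast.

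That size depends on p, which the document does not give, and on the assumed IRRs. The pattern is the same in both examples, but the figures are illustrations and do not predict this study's results. The loss of precision follows from having fewer exposed cases. Contamination of baseline is probable by the protocol's own reasoning about UTIs outside a definition, although this item does not address it, and its effect is modest (1.3 reading as 1.29 to 1.19).

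This is a cheap improvement to an exploratory analysis. The primary IRRs and the stated power are untouched.

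**What to change.** Keep every UTI that meets the primary definition as exposed. Class each episode as nitrofurantoin or other antibiotic, with a stated rule for episodes that have both. Fit one model, and report an IRR for each class and their ratio with a 95% CI from the interaction term, as the protocol already plans for organism.

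Retain the restricted run as a robustness check only, with the risk and prerisk periods of UTIs treated with other antibiotics kept out of baseline.

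State in advance that a ratio near 1 will not be read as no effect of antibiotic choice, because power for the contrast is limited. State also that any difference may reflect which UTIs receive nitrofurantoin.

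The cost is one extra exposure factor, built from prescription data that the primary definition already requires, and a sentence or two in the plan. No further data are needed.
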